### Sample size

The target study population consists of 250 IV-pensioners, who recently (not longer than a year) received the approval of the IV. In total, 126 persons were assigned to the intervention group, where they receive the coaching according to the IPS approach. The other 124 were assigned to the control group.

The sample size was calculated through power analysis. A medium effect size (0.42 SD) should be detected with a power of 95% at a two tailed significance level of 0.05.

Ideally, participants assigned to the intervention group can find employment in the competitive employment market and may subsequently become independent of social benefits subsequently.

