Firstly, IV-pensioners often lack the knowledge of the legal framework and are unsure about their rights. Erroneously, they commonly believe that they are not allowed to apply for a job in the competitive employment market while receiving an IV-pension. The IV-insurance is addressing this issue by providing more information to their pensioners. Secondly, pensioners grow accustomed to not working, thereby increasing the risk of further chronification. To minimize such risks this study includes only new IV-pensioners who have received an IV-pension for less than one year.

During the 1980s the concept of supported employment (SE) was developed in the USA [18] as a reaction to the inefficient *first train*, *then place*-models [19]. SE includes intensive job-search assistance for people with mental illness. Particular attention is given to the clients’ preferences and skills, to assist successful integration into the competitive employment market and to support them while working in competitive employment market [20]. In the USA this approach has been proven to be very successful [21]. However, a transfer of these methods to Europe requires certain structural changes, as Europe differs from the USA concerning job market and welfare system. In 2007 EQOLISE (Enhancing the Quality of Life and Independence of Persons Disabled by Severe Mental Illness through Supported Employment, [19]) was established. In this study, the first of its kind in Europe, participants were trained by job coaches according to the supported employment approach of Individual Placement and Support (IPS) [22]. This study was implemented in six centres across Europe. The results showed that participants assigned to the IPS group were employed more often into competitive employment as compared to the control group. In addition, the IPS participants dropped out of the study less often, and the rates of hospitalization were lower.

Moreover, EQOLISE demonstrated that working in a sheltered work place did not lead to a comparable stabilization of the affected persons [19]. A better state of mental health (e.g. lower anxiety and depression) and a more successful integration into the competitive employment market through the approach of IPS was evident [23].

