### Plan of analysis

This study aims to determine, whether job coaching according to IPS enables the successful integration of IV-pensioners into competitive employment.

The total N of this study is 250 participants. Through a Bernoulli randomization the participants are assigned to either the control or the intervention group.

The intervention’s effectiveness is tested by interview based instruments (in total 16 questionnaires). Binary, nominal and interval-scaled data are collected.

A two-factor analysis of variance with the two factors *group* (intervention versus control group) and *outcome* (employment yes/no) will be conducted to control the effectiveness of the intervention. The main criterion of the two-factor analysis will be the quantity of jobs received.

As parameters vary on more than one level a simultaneous comparison in a multilevel model is carried out.

Moreover, the study contains two group comparisons. The persistence of being employed or not in both groups is examined with help of a Cox-regression.

A significance level < 0.05, thus, a confidence interval of 95% is to be achieved.

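### With 126 and 124 participants, a simple two-group comparison has about 91% power for 0.42 SD at two-tailed 0.05, not the stated 95%

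*Protocol article*

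**What the plan says.** All the figures stand in the protocol article under Sample size. The size of the trial is given as "The target study population consists of 250 IV-pensioners". The split is given as "In total, 126 persons were assigned to the intervention group" and "The other 124 were assigned to the control group". The section says that the number came from a power analysis and then gives the target: "A medium effect size (0.42 SD) should be detected with a power of 95% at a two tailed significance level of 0.05".

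The Plan of analysis repeats the total ("The total N of this study is 250 participants"). It sets significance at 0.05 with a 95% confidence interval, which agrees with two-tailed testing. Neither section names the test behind the power analysis, and neither mentions an adjustment that would link these inputs to 250.

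**The concern.** For a comparison of two groups, the sample size, standardised effect, significance level and number of tails together fix the power. The article states all five quantities, so they can be checked against each other. A standard calculation with these inputs asks for nearly 300 participants rather than 250.

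At stake is how a null result would be read. A claim of 95% power tells the reader that a true effect of 0.42 SD would be missed one time in twenty. If the real figure is about one in eleven, a non-significant result would be given somewhat more weight than the design supports. The Discussion links the trial's result to whether IPS might be offered routinely to new pensioners, so the stated error rate should be right.

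**Working it through.** **Inputs** (all from Sample size): n₁ = 126, n₂ = 124, d = 0.42 (SD set to 1), two-tailed α = 0.05, stated power 0.95. Normal quantiles: z₀.₉₇₅ = 1.960, z₀.₉₅ = 1.645.

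**1. Power at the stated inputs.**
- Standard error of the standardised difference: √(1/126 + 1/124) = √0.0160 = 0.1265.
- Expected test statistic: 0.42 / 0.1265 = 3.320.
- Two-tailed power: Φ(3.320 − 1.960) = Φ(1.360) = 0.913.
- With the noncentral t distribution: 0.911.

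The stated 95% is not reproduced. The type II error is 1 − 0.911 = 8.9%, against the 5% implied.

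**2. Sample size for 95% power, two-tailed.**
- n per arm = 2(1.960 + 1.645)² / 0.42² = 147.3, so 148 per arm (296 in total).
- With the t distribution: 148.3, so 149 per arm (298 in total).
- 298 is 48 more than 250, or 19%.

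**3. Effect that 126 and 124 detect with 95% power, two-tailed.** With the t distribution, 0.458 SD.

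**4. Which variants reproduce the stated figure?** All use 126 and 124, or 125 per arm.

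| Calculation | Power |
|---|---|
| t test, two-tailed 0.05 | 91.1% |
| One-way F test, f = 0.21 | 91.1% |
| Wilcoxon, two-tailed, relative efficiency 0.864 to 0.955 | 87% to 90% |
| Two proportions, two-tailed, Cohen's h = 0.42, assumed control rates 10% to 50% | 90.5% to 91.4% |
| t test, one-tailed 0.05 | 95.2% |

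A continuity correction for two proportions raises the two-tailed requirement to 156 to 164 per arm, which is further from 250.

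For the one-tailed test, n per arm = 2(1.645 + 1.645)² / 0.42² = 122.7, so 123 per arm (246 in total). With the t distribution it is 123.4, so 124 per arm (248 in total). This agrees with a target of 250.

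**5. What a two-tailed calculation would need to reach 95% at n = 250.** The variance would have to fall to (0.42 / 0.458)² = 0.84 of its unadjusted value.
- Baseline adjustment: 1 − r² = 0.84, so a correlation r of about 0.40. For comparison, r = 0.3 gives 93.4% power and r = 0.5 gives 96.9%.
- Averaging four follow-up interviews: (1 + 3ρ)/4 = 0.84, so a within-person correlation ρ of about 0.79 or less.

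The article gives neither correlation. Both are back-calculated here only to show what would be needed.

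**The case against.** The strongest reply is that the article does not name the test behind the power analysis. It describes interviews at five time points (Recruitment and design, Table 1) and mentions a multilevel model (Plan of analysis). A gain from baseline adjustment or repeated measures could bring a two-tailed test to 95% under moderate correlations, as step 5 shows. This stands as a limit on the explanation: the one-tailed match is the only one among the standard unadjusted tests tried, but not the only conceivable one. It does not rescue the sentence, because the article neither states such an assumption nor ties one to the power analysis.

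It can also be said that 91% is good power, that recruitment had ended by September 2012, and that the planned confidence intervals will show precision whatever power was claimed. All of this stands, and it lowers the severity.

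A reader might infer three stronger points, which the document does not support:
- *A one-tailed calculation was made and misreported.* The arithmetic suggests this, but no passage says so.
- *The true power is lower still, because loss to follow-up was ignored.* The Background says of an earlier European trial that "the IPS participants dropped out of the study less often", but it gives no rate, and that is another study. An attrition allowance may sit in the full protocol, which is not shown.
- *No employment rates lie behind an effect given in SD units.* Not reporting rates in an article does not show that none were used. The stated main criterion is a count of contracts or jobs (Abstract, Plan of analysis), and a standardised difference is not contradictory for a count. For the same reason, no pair of employment rates can be read off as the trial's target.

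**Conclusion.** Wrong as written; should-fix. The stated sample size, effect, power and number of tails are mutually inconsistent for a simple two-group comparison. The power is about 91% rather than 95%, a gap of about 4 percentage points, and 95% would need about 298 participants rather than 250. The result assumes an unadjusted comparison of two groups with data from all 126 and 124 participants. A one-tailed calculation is a plausible cause, not an established one, and the inconsistency stands whatever the cause. The trial is not underpowered by usual standards on these figures, and no analysis, significance level or interval changes.

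**What to change.** Replace the power sentence under Sample size with, for example: *With 126 and 124 participants, the power for 0.42 SD is 91% at two-tailed 0.05 (95% power for 0.46 SD).* If the original calculation did rest on a further assumption, such as a covariate or repeated-measures gain, state it with its value so that the 95% can be reproduced.

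Keep the test two-tailed, in line with the Plan of analysis, and recruit no one further. The cost is one corrected sentence and a slightly less favourable stated power.

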### Inclusion and exclusion criteria

Inclusion criteria:

● IV-pension due to a mental disorder (full or part time pension)

● The participant does not receive the IV-pension for longer than a year

● The IV-pensioner`s goal is to work in the competitive employment market

● Ability to give written informed consent

● Working age (18–60)

Exclusion criteria:

● Organic mental disorder (-10: F0)Diagnosed to ICD

● Mental retardation (Diagnosed to ICD-10: F7)

### Interview based instruments and data collection

Based on the EQOLISE study the following instruments (German version) are used to quantify the outcome of the general well-being of the IV-pensioners. The participants are interviewed every 6 months by research workers (T_0_-T_4_).

(1) Incentive Focus Scale (IF): assessment of the participant`s motivation [25]

(2) Client Sociodemographic and Service Receipt Inventory (CSSRI- EU): assessment of sociodemographic facts and the medical supply [26,27]

(3) Lancashire Quality of Life Profile (LQoLP): assessment of the participant`s quality of live [28]

(4) Symptom-Checklist 90-Revised (SCL-90-R): assessment of the participant`s psychological symptoms [29]

(5) Rosenberg self-esteem scale (RSES): assessment of the participant`s self-esteem [30]

(6) Groningen Social Disability Scale (GSDS-II): assessment of social disabilities, fulfil their social role as expected [31]

(7) Global Assessment of Functioning (GAF): brief assessment of social, occupational and psychological functioning of the participant [32]

(8) Recovery Assessment Scale (RAS), 24-item short version: assessment of participant`s feeling towards him/herself and his/her life [33]

(9) Center for Epidemiological Studies Depression Scale (CES-D), German 15-item version: assessment of depressive symptoms [34]

This study will also assess stigma and recovery variables, using the following validated self-report measures administered once a year (T_0_, T_2_ and T_4_):

(1) Internalized Stigma of Mental Illness Scale (ISMI), 29 items [35]

(2) Cognitive appraisal of stigma as a stressor, 8 items [12,13]

(3) Perceived Devaluation-Discrimination Questionnaire (PDDQ), 12 items, measuring perceived public stigma [36]

Additionally, for those who worked at least one day in the last year.

Experienced discrimination at work, 5 items ([name] et al., unpublished). Furthermore, job preferences as well as the participant`s expectation concerning the process of finding an employment will be evaluated in the first interview (T_0_). Every six months (T_0_-T_4_) the current situation of employment and, if applicable, the participant`s satisfaction with his/her employment are assessed.

(1) Client Job Status: statement of the ongoing working situation of the participant

(2) Job Preferences: assessment of the participant`s job preferences

(3) Indiana Job-Satisfaction/Termination Scale (IJSS/IJTS): assessment of the participant`s satisfaction with his/her employment at the beginning, while having a job and if applicable after termination of her/his contract of employment

Moreover, job coaches are required to complete the IPS-Fidelity scale [37] every three months to ensure that the standards of the IPS concept are fulfilled.

### Plan of analysis

This study aims to determine, whether job coaching according to IPS enables the successful integration of IV-pensioners into competitive employment.

The total N of this study is 250 participants. Through a Bernoulli randomization the participants are assigned to either the control or the intervention group.

The intervention’s effectiveness is tested by interview based instruments (in total 16 questionnaires). Binary, nominal and interval-scaled data are collected.

A two-factor analysis of variance with the two factors *group* (intervention versus control group) and *outcome* (employment yes/no) will be conducted to control the effectiveness of the intervention. The main criterion of the two-factor analysis will be the quantity of jobs received.

As parameters vary on more than one level a simultaneous comparison in a multilevel model is carried out.

Moreover, the study contains two group comparisons. The persistence of being employed or not in both groups is examined with help of a Cox-regression.

A significance level < 0.05, thus, a confidence interval of 95% is to be achieved.

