### Recruitment and design

Persons who recently received the approval of the IV-pension were invited to an information event. The aim was to inform about the project as well as the supported employment concept IPS. Additionally the job coaches were introduced to the potential participants.

Those interested in participating in our study had the possibility to register and were invited to an one-on-one dialog for further information. Persons who subsequently wished to participate in the study signed the informed consent and were randomized to one of the two groups (control group or the intervention group). During the following two years the participants will be interviewed every six months concerning their well-being, self-esteem, stigma and recovery variables as well as job status (T_0_-T_4_) (List of instruments see Table 1).

**Table 1 T1:** Overview questionnaire based instruments

**Instrument**	**Variable**	**Perspective**	**Measurement point**				
			**T0**	**T1**	**T2**	**T3**	**T4**
Incentive focus scale	Motivation of participant	P	√	√	√	√	√
Client Sociodemographic and Service Receipt Inventory	Sociodemographic facts; medical supply	P/R	√	√	√	√	√
Lacanshire Quality of Life Profile	Quality of Life	P/R	√	√	√	√	√
Symptom checklist 90-revised	Psychological symptoms	P/R	√	√	√	√	√
Rosenberg self esteem scale	Self-esteem	P/R	√	√	√	√	√
Groningen Social Disability Scale	Social role; social disability	P/R	√	√	√	√	√
Global Assessment of Social Disability Scale	Overall psychological disturbance	R	√	√	√	√	√
Internalizes Stigma of Mental Illness Scale	Stigma coping; social drawback	P	√		√		√
Cognitive appraisal	Cognitive appraisal Stigmatization as stressor	P	√		√		√
Perceived Devaluation-Discrimination Questionnaire	Experienced Stigmatization	P	√		√		√
Recovery Assessment Scale	How they feel about themselves and their life	P	√		√		√
Centre für Epidemiological Studies Depression Scale	Depressive symptoms	P	√		√		√
Job discrimination	Experienced discrimination at working place	P	√		√		√
Client Job Status	Working situation	P/JC	√	√	√	√	√
Job Preferences	Job preferences	P/JC	√				
Indiana Job Satisfaction/ Termination Scale	Job satisfaction beginning, while and at the end	P/JC	√	√	√	√	√

*Note*: P: participant, R: Researcher, P/R: Patient by communicating with researcher, P/JC: Patient by communication with job coach; Measurement point: compiled every six month (T0, T1, T2, T3, T4).

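### The one effectiveness model the protocol spells out has no baseline term, so the scale outcomes lose precision and protection against chance imbalance that their T0 scores could give

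*Protocol article*

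**What the plan says.** The protocol article, Plan of analysis, specifies one effectiveness model: "A two-factor analysis of variance with the two factors *group* (intervention versus control group) and *outcome* (employment yes/no) will be conducted". The Abstract and the section Recruitment and design name the same two factors. The main criterion of this model is the number of jobs obtained.

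The same section also says: "The intervention’s effectiveness is tested by interview based instruments (in total 16 questionnaires"). The word main, together with this sentence, implies that scale scores are compared between the groups as well. Research questions 2 and 6 concern quality of life, mental health, self-esteem, stigma and recovery.

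A multilevel model and a Cox regression follow, each in one sentence. Neither sentence lists the model's terms.

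On allocation the section says: "Through a Bernoulli randomization the participants are assigned to either the control or the intervention group". No stratification factor is named.

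On measurement, Recruitment and design says: "During the following two years the participants will be interviewed every six months concerning their well-being, self-esteem, stigma and recovery variables as well as job" (that is, the employment situation). Table 1 ticks T0 for all 16 instruments, and T4 for every one except Job Preferences.

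**The concern.** A person's score on a quality-of-life, symptom or stigma scale usually resembles the same person's score two years earlier. If follow-up scores are compared without the T0 score, that stable between-person variation stays in the error term. Any chance difference between the groups at T0 also passes in part into the estimated effect of IPS. Simple randomisation does nothing to limit such a difference on a prognostic variable, and the stated model does not correct for it.

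The protocol itself treats some T0 variables as prognostic. The Background expects higher stigma to go with poorer IPS results, and research questions 5 and 7 look for predictors of success.

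At stake are precision and protection against imbalance on the scale outcomes, most of all for effects below 0.42 SD. Recruitment is complete and the participants are assigned, so the analysis is the only remaining place to use this information.

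**Working it through.** **Inputs.** Sample size section: "A medium effect size (0.42 SD) should be detected with a power of 95% at a two tailed significance level of 0.05"; "In total, 126 persons were assigned to the intervention group"; "The other 124 were assigned to the control group". The correlation ρ between T0 and follow-up scores is not given, so it is assumed to lie between 0.3 and 0.7. No dropout is applied.

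**Step 1: the plan's own figure.** By the normal approximation, n per arm = 2 × ((1.960 + 1.645) / 0.42)² = 147.3, so 148 per arm and 296 in total. The stated 250 is not reproduced. This mismatch is a separate point; here it only sets the starting power.

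**Step 2: unadjusted power at the actual size.** The standard error of a mean difference, in SD units, is √(1/126 + 1/124) = 0.1265. The noncentrality is 0.42 / 0.1265 = 3.32. With 248 degrees of freedom the two-sided t test has 91.1% power (normal approximation 91.3%).

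**Step 3: power with the T0 score as covariate.** The residual SD becomes √(1 − ρ²), so the noncentrality is 0.42 / (0.1265 × √(1 − ρ²)), with 247 degrees of freedom. The 95% CI half-width is 1.97 × 0.1265 × √(1 − ρ²).

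| Assumed ρ | Residual variance | Noncentrality | Power at 0.42 SD | CI half-width (SD) |
|---|---|---|---|---|
| 0 (unadjusted) | 1.00 | 3.32 | 91.1% | 0.25 |
| 0.3 | 0.91 | 3.48 | 93.4% | 0.24 |
| 0.4 | 0.84 | 3.62 | 95.0% | 0.23 |
| 0.5 | 0.75 | 3.83 | 96.9% | 0.22 |
| 0.7 | 0.51 | 4.65 | 99.6% | 0.18 |

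By the normal approximation, the total needed for 95% power is 296 × (1 − ρ²) before rounding up to whole arms. At ρ = 0.4 that is 248, so at this correlation or above the existing sample would reach the stated 95% on a scale outcome.

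**Step 4: a smaller effect.** For a true effect of 0.30 SD, power is 66% unadjusted and 78% at ρ = 0.5.

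**Step 5: chance imbalance.** The T0 mean difference also has standard error 0.1265 SD, so 95% of allocations fall within 1.96 × 0.1265 = 0.25 SD. With equal SDs, an imbalance of 0.25 SD left unadjusted shifts the follow-up difference by ρ × 0.25, which is 0.075, 0.125 or 0.175 SD at ρ = 0.3, 0.5 or 0.7. The middle value is 0.125 / 0.42 = 30% of the planned effect.

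**Scope.** Steps 2 to 5 apply to an interval-scaled outcome that has its own T0 score. The number of jobs obtained after randomisation has no such score, and the documents give nothing from which its gain could be computed.

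**The case against.** The main criterion of the quoted model is the number of jobs, and none of the figures above applies to it. The 16 questionnaires include Client Job Status, so the sentence about them does not prove that the scale scores are dependent variables of this ANOVA. This stands in part. That scales are compared is an inference, although the word main and research questions 2 and 6 make it a reasonable one. The computed gains must be confined to the scales.

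A reader might infer that the whole effectiveness analysis lacks baseline adjustment. The document does not support that. The multilevel and Cox models have unspecified terms, and either could carry T0 values. Covariate lists are also commonly left to an analysis plan, which is not shown here. What can be criticised is the model whose factors are listed, and that list has no baseline term.

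A reader might also infer that the unadjusted comparison is biased. It is not. Over repeated randomisations a comparison of the randomised groups is unbiased and has the correct type I error. The loss is one of precision, and of protection in the particular allocation that occurred.

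Nor does every outcome have a usable T0 score. Job satisfaction is assessed only if applicable, and discrimination at work only for those who worked in the past year.

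Finally, the same sentence has a more serious fault: employment, a post-randomisation outcome, is used as a factor. Baseline adjustment does not cure that, and it needs its own correction.

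**Conclusion.** The point holds for the well-being, symptom, self-esteem, disability, stigma, recovery and depression scales. The only effectiveness model with listed terms leaves out T0 scores that the trial collects, and unstratified allocation leaves chance imbalance uncorrected.

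At the planned effect the cost is about 2 points of power if ρ is 0.3, nearly 6 if it is 0.5 and 8.5 if it is 0.7. The gain reaches 5 points only at ρ of about 0.5 or more. It is larger for smaller effects: 12 points at 0.30 SD and ρ = 0.5 (65.6% to 77.9%). The size rests on the assumed ρ, on full follow-up, and on applying 0.42 SD to a scale, which the protocol does not itself do.

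For the number of jobs, prognostic T0 covariates are sensible, but no gain is claimed. This is an inexpensive improvement that should be made; it is not a threat to validity.

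**What to change.** In Plan of analysis, add the following:

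- Each scale outcome with a T0 score is compared between the randomised groups with that score as a covariate, either by ANCOVA at T4 or in the multilevel model on the follow-up visits.
- The group comparison on the employment criterion includes a short prespecified set of T0 covariates already collected, such as Client Job Status and motivation (Incentive Focus Scale).
- The unadjusted estimate is reported as a sensitivity analysis.
- Job satisfaction and discrimination at work, which apply only to people who have worked, are outside this rule.

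The cost is one or two sentences, with no new data and no extra participants. The drawback is that a participant with a missing T0 score needs simple baseline imputation to stay in the model.

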**Method/design:**

The present pilot project ZHEPP (Zürcher Eingliederungs-Pilot Projekt; engl.: Zurich integration pilot project) is a randomized controlled trial (RCT). The 250 participants will be randomized to either the intervention or the control group. The intervention group receives support of a job coach according to the approach of IPS. Participants in the control group do not receive IPS support. Participation takes a total of two years for each participant. Each group is interviewed every six months (T_0_-T_4_). A two-factor analysis of variance will be conducted with the two factors *group* (intervention versus control group) and *outcome* (employment yes/no). The main criterion of the two-factor analysis will be the number of competitive employment contracts in each group.

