### Research question

The main aim of this study is:

(1) To determine if job coaching according to the IPS approach leads to a more successful integration of new IV-pensioners into competitive employment.

In addition, the following issues will be analyzed:

(2) Possible enhancement of quality of life, state of mental health and level of self-esteem by finding competitive employment

(3) Chances of maintaining an employment and increasing the workload, if the participant desires this and has the ability

(4) Cost-benefit equation of job coaching and potential saving schemes as compared to the current handling

(5) Predictors for a successful coaching after receiving an IV-pension

(6) The effect of IPS on stigma variables (perceived public stigma, self-stigma, stigma stress) and recovery orientation

(7) Stigma variables and recovery orientation as predictors of finding competitive employment during IPS

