The ZHEPP project is a randomized control trial (RCT) with two factors, *group* (intervention versus control group) and *outcome* (employment yes/no).

The participants of the intervention group are supported by a job coach according to the approach of IPS. Those randomized to the control group are not subject to any intervention by our job coaches, but are merely invited to an interview every six months. The catchment area is the canton of Zurich, Switzerland.

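### The main effectiveness analysis is mis-specified: employment yes/no, which is the result of the intervention, is entered as an explanatory factor in an ANOVA of the number of jobs

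*Protocol article*

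**What the plan says.** The main aim, under Research question, is "To determine if job coaching according to the IPS approach leads to a more successful integration of new IV-pensioners into competitive employment".

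The test of effectiveness is given in Plan of analysis: "A two-factor analysis of variance with the two factors *group* (intervention versus control group) and *outcome* (employment yes/no) will be conducted". The dependent variable follows: "The main criterion of the two-factor analysis will be the quantity of jobs received".

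The abstract repeats the model ("A two-factor analysis of variance will be conducted with the two factors" of group and outcome) and words the criterion slightly differently: "The main criterion of the two-factor analysis will be the number of competitive employment contracts in each group". Recruitment and design presents the same pair as a feature of the trial itself: "The ZHEPP project is a randomized control trial (RCT) with two factors", namely group and employment yes/no.

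Plan of analysis also mentions a multilevel model, without naming its outcome, and a Cox regression on how long participants in the two groups remain in or out of work. It states no direct comparison of the proportion employed by arm.

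**The concern.** Group is assigned by randomisation. Employment arises afterwards and is what coaching is intended to change. The plan nevertheless places it on the explanatory side, next to group, to explain a job count that it largely determines.

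Two things follow. First, adjusting the group comparison for employment removes the effect that the trial was set up to find. What remains is a comparison among employed people, a subset selected by the effect of treatment and so no longer protected by randomisation. Second, two of the four cells (not employed, in either arm) contain only zeros. Their variance is zero, and the pooled error term of the ANOVA is wrong for most of the contrasts one might test.

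The Discussion says that a supported hypothesis may lead to IPS being offered routinely to new pensioners. A main test that does not measure entry into work could miss a real benefit, or report one when only job-changing differs.

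**Working it through.** **Inputs from the article.** Arms of 126 and 124, a two-tailed level of 0.05 and an effect of 0.42 SD (Sample size); factors and criterion as quoted above. No employment rates and no distribution of jobs are given, so those below are assumptions.

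**The plan's own figure.** The only related figure is N = 250 for 0.42 SD "with a power of 95% at a two tailed significance level of 0.05". For two means, n per arm = 2(1.960 + 1.645)²/0.42² = 25.99/0.1764 = 147.3, so 148 per arm and 296 in total. The figure of 250 is close to the one-sided result: 2(1.645 + 1.645)²/0.1764 = 122.7, so 123 per arm and 246 in total. This is a separate matter and nothing below depends on it.

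**Step 1: what the group term estimates.** Let m_I and m_C be the mean jobs per employed person in the two arms. The four cell means are 0, 0, m_I and m_C.
- *Full factorial (Type III):* group effect = ½[(0 − 0) + (m_I − m_C)]. The interaction is the same contrast, so the two tests coincide.
- *Additive (group adjusted for employment):* a weighted average of 0 and (m_I − m_C).
- *Sequential, group first (Type I):* the difference in overall mean jobs, which does depend on the employment rates.

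The first two do not contain the difference in employment proportions. If m_I = m_C, they estimate zero whatever coaching does for employment. If every employed person holds exactly one job, the residual variance is zero and F is undefined.

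**Step 2: error rate under no effect.** Let p be the common employment rate, and m and s² the mean and variance of jobs among the employed. The pooled error variance is about p·s², because the unemployed cells contribute nothing. With equal arms, the ratio of true to assumed variance is:
- additive: 1, so the level is about 5%;
- full factorial: (1 − p)/p;
- sequential, group first: 1 + (1 − p)m²/s².

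The rejection rate is P(|Z| > 1.96/√ratio). Assume jobs = 1 + Poisson(0.4), so m = 1.4, s² = 0.4 and m²/s² = 4.9.

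| p | Full-factorial ratio | Rejects | Sequential ratio | Rejects |
|---|---|---|---|---|
| 0.20 | 4.00 | 33% | 4.92 | 38% |
| 0.30 | 2.33 | 20% | 4.43 | 35% |
| 0.391 | 1.56 | 12% | 3.98 | 33% |

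**Step 3: simulation.** 126/124, 2,000 to 4,000 trials per scenario, same job model in both arms. Ranges cover repeat runs. The pair 39.1% v 20% was chosen because 2·arcsin√0.391 − 2·arcsin√0.20 = 0.42.

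| Employment, IPS v control | Chi-square | Additive | Full factorial | Sequential |
|---|---|---|---|---|
| 39.1% v 20% | 92% | 4% | 21-23% | 98% |
| 20% v 20% | 5% | 5% | 34-35% | 31-40% |
| 30% v 30% | 5% | 5% | 21-23% | 31-40% |
| 39.1% v 39.1% | 5% | 5% | 11-12% | 31-40% |

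The sequential range is given across all three no-effect rows.

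**Step 4: range of assumed effects.** With jobs = 1 + Poisson(0.2) or 1 + Poisson(0.5), for control v IPS rates of 10% v 20%, 15% v 30%, 20% v 40% and 30% v 50%:
- direct comparison of proportions: power 60%, 81%, 94% and 90%;
- employment-adjusted group test: 3-6% throughout;
- full factorial: 44%, 30-31%, 21-22% and 12%, so it does not track the effect;
- sequential: 87-99%, but 38-46% at 20% v 20%.

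**Step 5: equal employment, more job changes.** With 30% employed in both arms and means of 2.0 v 1.3 jobs per employed person, the additive test rejects in 96-97% and the full factorial in about 99%; chi-square stays at 4-5%. With 1.6 v 1.2 jobs, the additive test rejects in 79-80% and the full factorial in 94-95%.

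**The case against.** Four objections carry weight.

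*The ANOVA can react to employment.* A reader might infer that the stated analysis cannot detect an effect on employment at all. The article does not support that. It does not fix the type of sums of squares, which an article may leave to an analysis plan, and the sequential test with group first rejects in 98% at 39% v 20%. This stands as a limit on the claim. It does not rescue the analysis, because the same test rejects in 31-40% when employment is equal.

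*The full-factorial result is not simply the same with and without an effect.* A reader might take 21-23% at 39% v 20% and 21-23% at 30% v 30% as showing that. The match depends on the null rate chosen: 34-35% at 20% and 11-12% at 39%. What is established is an uncontrolled error rate.

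*A 2x2 comparison may have been meant.* The abstract speaks of a count of contracts per group, and with employment yes/no this could be a badly described group-by-employment table. The zero-variance argument would then not arise. But Plan of analysis names an analysis of variance with a separate job-count criterion, and on the 2x2 reading the text still needs correcting.

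*Other analyses are planned.* The Cox regression could be read as including time out of work until a first job, which would bear on the main aim. Its wording is too loose to settle this, the multilevel model has no stated outcome, and neither is given as the main test of effectiveness.

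The article also says main criterion rather than primary analysis. The ANOVA is nonetheless the one analysis that it ties to the effectiveness of the intervention.

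**Conclusion.** The point holds as a mis-specification. The article describes, consistently in three places, a main analysis that conditions on the result of treatment and so does not validly test the stated main aim. This is a wrong statement rather than an omission that an analysis plan might fill.

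The structural part needs no assumption about rates: in the adjusted and full-factorial models the group contrast contains only jobs per employed person. The sizes are illustrative and rest on assumed employment rates and a 1 + Poisson job count. On those assumptions the additive test stays at about 4-5% with or without an employment effect, against 92% for chi-square at 39% v 20%. The full-factorial test rejects in about 11-34% under no effect, and the sequential test in about 31-40%. No version both holds 5% and tests entry into work.

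It does not follow that the trial cannot answer its question. The design and the data collected allow a valid comparison.

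**What to change.** - Delete outcome as a factor in the abstract, in Recruitment and design and in Plan of analysis.
- Make competitive employment yes/no the dependent variable and randomised group the design factor. Compare the arms by intention to treat, as a difference in proportions with 95% confidence interval and chi-square test, or by logistic regression. State the time point or period over which employment is counted.
- Make number of jobs a secondary outcome, compared by randomised group without conditioning on employment.
- Adjustment for job status at T0 is optional.
- If a group-by-employment 2x2 comparison was intended, describe it as that and drop the term analysis of variance.

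The cost is wording only. Table 1 already schedules Client Job Status at every interview from T0 to T4, so no new data and no further participants are needed. The change should be recorded before outcome data are compared by arm.
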